# Central mechanisms of real and sham electroacupuncture in the treatment of chronic low back pain: study protocol for a randomized, placebo-controlled clinical trial

**DOI:** 10.1186/s13063-018-3044-2

**Published:** 2018-12-13

**Keywords:** Chronic, Low back pain, Electrical acupuncture, Electroacupuncture, Sham acupuncture, Quantitative sensory testing, Temporal summation, Expectation, Conditioned pain modulation, Pressure pain threshold, Catastrophizing, Self-efficacy, PROMIS

## Abstract

**Background:**

Chronic low back pain (CLBP) is the most common chronic pain condition and is often resistant to conventional treatments. Acupuncture is a popular alternative for treating CLBP but its mechanisms of action remain poorly understood. Evidence suggests that pain regulatory mechanisms (particularly the ascending and secondarily the descending pain modulatory pathways) and psychological mechanisms (e.g., expectations, pain catastrophizing and self-efficacy) may be involved in the pathogenesis of CLBP and its response to treatments. We will examine these mechanisms in the treatment of CLBP by electroacupuncture (EA).

**Methods:**

We present the aims and methods of a placebo-controlled, participant-blinded and assessor-blinded mechanistic study. Adult patients with CLBP will be randomized to receiving 16 sessions of real (active) or sham (placebo) EA over the course of 8 weeks. The primary pain regulatory measure for which the study was powered is temporal summation (TS), which approximates ascending pain facilitation. Conditioned pain modulation (CPM), representing a descending pain modulatory pathway, will be our secondary pain regulatory measure. The primary psychological measure is expectations of benefit, and the secondary psychological measures are pain catastrophizing and self-efficacy in managing pain. Main clinical outcomes are back pain bothersomeness on a 0–100 visual analog scale (primary), Roland Morris Disability Questionnaire (secondary), and relevant items from the National Institutes of Health (NIH) Patient-Reported Outcome Measures Information System (secondary). We hypothesize that compared to sham, real EA will lead to greater reduction in TS after 8 treatment sessions (4 weeks); and that reduction in TS (and secondarily, increase in CPM) after 8 treatment sessions will mediate reduction in back pain bothersomeness from baseline to week 10 (clinical response) to EA. We also hypothesize that the three psychological factors are moderators of clinical response. With 100 treatment completers, the study is designed to have 80% power to detect a medium-sized between-group effect (*d* = 0.5) on temporal summation.

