#### Sample size

We computed the sample size based on detecting differential changes in TS, the primary mediator. A small pilot study conducted in our laboratory suggested an average change of 10–25 points on the 100-point VAS with a standard deviation of 12 in TS following acupuncture. Prior studies suggest no treatment effect in controls receiving sham acupuncture [35]. However, given the imprecision of the pilot study estimates of effect sizes, we have elected to power the study to detect a medium-sized effect (*d* = 0.56) with 50 subjects in each arm, using the two-tailed test with alpha = 0.05 and beta = 0.8. If the point estimates from the pilot prove to be correct, this project will be very well-powered (98% power) to detect a large effect (*d* = 0.833). To account for attrition of about 20%, we plan to enroll about 120 study participants.

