##### Planned analysis

This hypothesis will be tested using the two-tailed, two-sample *t* test, comparing the change in TS from baseline to week 4 between the real and sham arms.

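### The abstract's 80% power at d = 0.5 with 100 completers is wrong: it is 70%, and the sample-size section uses d = 0.56, mislabels beta and falls short on attrition

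*Protocol article*

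**What the plan says.** The Methods paragraph of the abstract gives the design power: "With 100 treatment completers, the study is designed to have 80% power to detect a medium-sized between-group effect (*d* = 0.5) on temporal summation".

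The Sample size section gives a different effect for the same number of completers. Its stated target reads: "power the study to detect a medium-sized effect (*d* = 0.56) with 50 subjects in each arm". The test and the error rates are then given as follows: "using the two-tailed test with alpha = 0.05 and beta = 0.8". It adds that if the pilot estimates are right, power is 98% at d = 0.833. On enrolment it says: "To account for attrition of about 20%, we plan to enroll about 120 study participants".

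The test for hypothesis 1a is fixed under Statistical methods: "This hypothesis will be tested using the two-tailed, two-sample *t* test, comparing the change in TS from baseline to week 4". The same section makes the per-protocol completers the primary analysis sample (all three assessments and at least 13 of 16 treatment visits). Trial design gives equal allocation.

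**The concern.** Both places call the effect medium-sized and both rest on 100 completers, but one puts 80% power at d = 0.5 and the other at d = 0.56. With a fixed n, test and alpha, only one effect size can carry 80% power. The section that should settle the matter labels 0.8 as beta, which is the type II error. It also pairs an attrition rate with an enrolment figure that does not return 100 completers.

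Temporal summation (TS) is the measure for which the trial was powered, and the Discussion paragraph of the abstract calls the trial appropriately powered. A reader of the abstract would take it that a true d = 0.5 has a one-in-five chance of being missed. If the chance is nearer one in three, a null result on hypothesis 1a says less about effects of that size than the abstract implies.

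**Working it through.** **Inputs**

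| Input | Value | Source |
|---|---|---|
| Completers | 100, i.e. 50 per arm | Abstract; Sample size |
| Test | two-tailed two-sample t test on change in TS | Planned analysis, hypothesis 1a |
| Alpha | 0.05, two-tailed | Sample size |
| Effect size | 0.5 or 0.56 | Abstract; Sample size |
| Attrition, enrolment | about 20%, about 120 | Sample size |

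**Formula.** With n per arm, the noncentrality is d × √(n/2) on 2n − 2 degrees of freedom. The normal approximation to power is Φ(d√(n/2) − 1.96). The exact figure uses the noncentral t.

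**Step 1: reproduce the Sample size section.** For n = 50, √(50/2) = 5.
- d = 0.56: 0.56 × 5 = 2.80, and Φ(2.80 − 1.96) = Φ(0.84) = 80.0%. Noncentral t: 79.2%.
- d = 0.833 (10/12 from the pilot): 0.833 × 5 = 4.165, and Φ(2.205) = 98.6%. Noncentral t: 98.5%, against the stated 98%.

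Both figures reproduce, so the method is correctly identified.

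**Step 2: the abstract's figure.**
- d = 0.5: 0.5 × 5 = 2.50, and Φ(2.50 − 1.96) = Φ(0.54) = 70.5%. Noncentral t: 69.7%.
- Required n per arm: 2 × (1.96 + 0.8416)² / 0.5² = 62.8, so 63 by the normal approximation and 64 by t, i.e. 126 to 128 completers.
- Smallest effect with 80% power at 50 per arm (noncentral t): d = 0.566.

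**Step 3: could another reading give 80% at d = 0.5?**
- All 120 enrolled complete (60 per arm): 78.2% (normal), 77.5% (t). Still short.
- One-sided alpha 0.05: Φ(2.50 − 1.645) = 80.4% (normal), 79.9% (t). This matches, but both the Sample size section and the planned analysis specify a two-tailed test.

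**Step 4: beta = 0.8.** Read literally, this means 20% power. At d = 0.56 that needs 2 × (1.96 − 0.8416)² / 0.56² ≈ 8 per arm, not 50. The stated n, d and alpha fit only power = 0.8.

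**Step 5: attrition.** 120 × 0.8 = 96 completers. To keep 100 after 20% loss takes 100 / 0.8 = 125 enrolled. The figure 120 equals 100 × 1.2. Attrition that leaves 100 of 120 is 1 − 100/120 = 16.7%.

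**Step 6: power side by side (noncentral t, two-sided 0.05).**

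| Completers | d = 0.5 | d = 0.56 | d with 80% power |
|---|---|---|---|
| 100 (50 per arm) | 69.7% | 79.2% | 0.566 |
| 96 (48 per arm) | 67.9% | 77.5% | 0.578 |

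Type II error at d = 0.5 is 100 − 69.7 = 30.3% with 100 completers and 100 − 67.9 = 32.1% with 96.

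**The case against.** The section that sets the sample size is sound to rounding: d = 0.56 with 50 per arm gives 80.0% by the normal approximation. On this view the trial is not mis-sized. One abstract sentence carries the wrong effect size, and changing it to 0.56 would be enough. Writing beta for power is a labelling slip that did not affect n. The attrition text says about 20% and about 120, which can be stretched to cover 16.7%, and that 120 came from multiplying by 1.2 is an inference, since no derivation is shown. Finally, a null result would be judged from its estimate and confidence interval, not from design power.

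Much of this stands. The serious error is in the abstract, the beta label is a copy-edit, and the attrition point is small: at d = 0.56 it moves power only from 79.2% to 77.5%. A confidence interval is indeed the right way to read a null result.

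None of it rescues the abstract. Rounding does not turn 0.56 into 0.5, and the difference raises the type II error from about 20% to about 30%. The one reading that gives 80% at d = 0.5 is one-sided, which the protocol rules out. The abstract is also where most readers will find the power claim, and the attrition slip pushes power the same way.

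**Conclusion.** The concern holds. With the test, alpha and completers that the protocol fixes, power at d = 0.5 is 69.7%, about 10 percentage points below the stated 80%. It is 67.9% if 20% of 120 are lost. The effect for which 100 completers give 80% power is d = 0.566, so the Sample size section's 0.56 is approximately right and the abstract's 0.5 is not. The beta label is a slip with no effect on n. The attrition shortfall is 4 completers if the loss is exactly 20%, and nil if it is at most 16.7%.

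These figures assume equal arms among completers and an unadjusted two-sample t test on change in TS, as planned. They do not depend on the pilot standard deviation, because the plan states its effects as d.

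**What to change.** Use one power statement in the abstract and the Sample size section, for example: 100 completers (50 per arm) give 80% power for d = 0.57 and 70% for d = 0.5, with two-sided alpha 0.05 and power 0.8; enrolling 120 allows for 16.7% attrition, and at 20% attrition the 96 completers give 80% power for d = 0.58. Replace beta = 0.8 with power = 0.8 (or beta = 0.2). If the authors prefer to keep 0.56, they should say that it rests on the normal approximation and that the t test gives 79%.

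This is a text correction. Sample size, test, analysis set and conduct stay as they are; the only cost is a slightly less favourable power figure. Keeping the claim of 80% power at d = 0.5 would instead need 128 completers, or 128 / 0.8 = 160 enrolled at 20% attrition. That is not a realistic route, since Trial status expects recruitment to end within weeks of publication.

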**Discussion:**

To the best of our knowledge, this is the first appropriately powered, placebo-controlled clinical trial evaluating mechanisms of EA in the treatment of CLBP.

**Trial registration:**

ClinicalTrials.gov, NCT02503475. Registered on 15 July 15 2015. Retrospectively registered.

**Electronic supplementary material:**

The online version of this article (10.1186/s13063-018-3044-2) contains supplementary material, which is available to authorized users.

## Background

Chronic low back pain (CLBP) affects between 10 and 20% of adults [1], is the number one reason for missing work due to disability [2], and is the third most costly medical condition in the USA, after diabetes mellitus and ischemic heart disease [3]. The management of CLBP remains a significant challenge. Conventional, anatomically-based treatments such as surgical fusion and disc replacement often result in minimal or short-lived improvement [4]. Past research has determined that many patients with CLBP may have abnormalities in pain processing [5–7].

Electroacupuncture (EA) offers a promising alternative to conventional approaches in treating CLBP (i.e., drugs and surgery) and needs additional investigation. The majority of studies on acupuncture for CLBP have used manual acupuncture with equivocal results [8]. For example, both Haake (Germany) [9] and Cherkin (USA) [10] found that acupuncture led to greater improvement in pain and function compared with usual care (medical visits, physical therapy, and oral medications). However, neither study demonstrated a statistically significant difference between real and sham acupuncture. Pre-clinical and animal studies have suggested that EA might have stronger analgesic effects compared with manual acupuncture [11]. However, there is a relative paucity of studies on the effectiveness and even fewer studies on the mechanisms of EA in treating chronic pain conditions, particularly CLBP. Our study aims to address this gap by examining the differential mechanisms of real vs sham EA in the context of what is to the best of our knowledge, the largest randomized controlled, blinded study comparing the two treatments.

Central pain processing: the central processing of pain (i.e., nociceptive signals) has an ascending (peripheral to central) and a descending (central to peripheral) modulatory pathway [12–16]. There are both facilitatory and inhibitory inputs for each pathway. The final pain perception is the result of the integration of these complex bidirectional inputs from both the ascending and the descending pathways. Dysregulation in these pathways has been associated with CLBP [5, 6, 17]. Normalization of central pain processing [18–20] has been the mechanism purported to explain the success of several treatments for CLBP, including antidepressants, anticonvulsants, and cognitive behavioral therapy [21–23].

It is difficult to measure central pain processing directly in humans. Several experimental, non-invasive techniques have been used to infer central pain processing. One key technique is quantitative sensory testing (QST). It consists of administering standardized sensory stimuli to participants and measuring their ratings of the intensity of these stimuli and pain thresholds [24, 25]. Temporal summation (TS), to be used in this study as the primary mechanism outcome, is a specific QST measure that estimates ascending pain facilitation at the spinal cord level. Specifically, TS refers to increased pain perception to the application of a rapid sequence of identical noxious stimuli [26]. The increase in pain perception is considered a behavioral correlate of windup, a physiological process where wide-dynamic range (WDR) neurons in the spinal dorsal horn augment incoming rapid pain signals. Windup occurs when there is insufficient time for the stimulated WDR neurons to return to their baseline state before the next stimulus is applied [27, 28]. Windup is a key step in the ascending facilitation of pain transmission.

Secondarily, we will also assess conditioned pain modulation (CPM). CPM is a QST measure of the descending inhibitory central pain pathway. The CPM quantifies the extent to which the application of a second noxious stimulus reduces the perception of pain from a prior noxious stimulus [29]. In that way, CPM is considered the behavioral correlate of diffuse noxious inhibitory control, where a single, heterotopic noxious stimulus leads to brain-stem-mediated diffuse inhibition of subsequent incoming nociceptive transmission from elsewhere in the body [30]. Diffuse noxious inhibitory control is distinct from distraction [31].

Preliminary studies in animals and healthy human subjects suggest involvement of the central pain modulatory pathway in acupuncture analgesia [32]. For example, studies by Han [33] and Pomeranz [34] independently revealed that acupuncture, particularly electroacupuncture (EA), produces pain relief by augmenting descending pain inhibition via central opioidergic receptors at the periaqueductal gray and spinal dorsal horn. Similarly, Zheng et al. showed that acupuncture reduces ascending pain facilitation, as evidenced by decreases in TS from electrical pain induced in healthy volunteers [35]. They further showed that EA produces greater reductions in TS than manual acupuncture. Most of these studies were conducted on animals or healthy volunteers [36]. In this innovative study, we propose to investigate central mechanisms of acupuncture in a clinical population suffering from CLBP.

Expectations: several clinical studies have found that pretreatment expectation of benefits from treatment is a powerful predictor of pain reduction in response to treatments [37, 38]. Sherman et al. found that expectation following initial treatment might be more relevant to eventual outcome than pretreatment expectations [39]. In the present study, we will assess expectations both after (primary) and before (secondary) the first treatment session and examine both post first-session (primary) and pre first-session (secondary) expectations as moderators of clinical outcomes.

Additional (secondary) psychological factors: some data suggest that psychological and cognitive attributes, such as perceived self-efficacy in managing pain and pain catastrophizing, may also moderate clinical outcomes in response to pain treatment in general [40, 41] and acupuncture in particular [42]. Therefore, we will assess these two constructs and examine them as moderators of clinical outcomes.

### Specific aims and hypotheses

#### Aim 1

Aim 1 is to characterize the effect of TS (primary pain regulatory measure) as a mediator of reduction in back pain bothersomeness in response to treatment (primary clinical outcome). We hypothesize that:

(a) Compared to sham, real EA will lead to greater reduction in TS from baseline (week 0) to the end of week 4 (i.e., after 8 biweekly treatment sessions) (aim 1a)

(b) The change in TS from baseline to week 4 will mediate reduction in back pain bothersomess over the course of treatment (from baseline to post treatment (around week 10)) (aim 1b)

#### Aim 2

Aim 2 is to assess expectation of benefits (primary psychological measure) as a moderator of reduction in back pain bothersomeness in response to treatment (primary clinical outcome). We hypothesize that participants’ expectations of benefits will predict reduction in back pain bothersomeness scores during the treatment period (week 0 to week 10).

#### Aim 3 (exploratory)

Aim 3 is to assess aims 1 and 2 using secondary mediator and moderator variables of reduction in back pain bothersomeness from week 0 to week 10 (primary outcome) and the reduction in secondary clinical outcome measures over the same time frame. Hypotheses to be tested are identical to the hypotheses for aims 1 and 2, replacing the primary mediator with secondary mediators and primary moderators with secondary moderator variables.

##### Clinical impact

This clinical trial aims to delineate pain regulatory and psychological mechanisms of real (active) versus sham (placebo) EA in treating CLBP. The primary mechanisms investigated in this study are ascending pain facilitation estimated by TS, a specific measure from quantitative sensory testing, and expectations of benefit from the intervention, a psychological measure. The primary clinical outcome in this mechanistic study is back pain bothersomeness. While we will provide results on comparative efficacy of the real and sham EA in treating CLBP, our primary focus is on mechanisms and predictors of the clinical outcomes.

The results of this mechanistic study could have future clinical care implications because they will inform on the potential contribution of pain regulatory processes (mediator) and expectation of benefit (moderator) to clinical outcome. Identification of mediators of clinical response could help guide selection of patients who are most likely to respond to EA. For example, those with deficits in a given mediator variable, such as those with temporal summation deficit may potentially have better response to acupuncture. Identification of moderators will help guide decisions about targets to enhance clinical outcome. For example, we can potentially augment clinical outcome from acupuncture by an intervention to enhance expectation of benefits.

## Methods

### Trial design

In this randomized, placebo-controlled clinical trial each participant will have an equal chance (50%) of being randomized to receive real or sham EA. Our goal is to examine the pain regulatory mechanisms of real (active) and sham (placebo) EA in treating CLBP and evaluate the role of expectations of benefit and other psychological variables in moderating clinical response.

### Explanation for choice of comparators

We will include a parallel, placebo control in the form of sham EA because in order to assess the specific effects of acupuncture, we need to control for the nonspecific effects of acupuncture [43, 44]. We are interested in elucidating both the nonspecific (delivered by sham and real EA) and the specific (delivered by real EA) elements of acupuncture analgesia.

### Study setting

This is a single-site study. Study screening, enrollment, and procedures will take place at the Stanford Center for Back Pain Laboratory. Acupuncture treatment administration will take place at community acupuncture clinics in the larger San Francisco Bay Area.

### Participants

The Inclusion criteria are:Men or women between the ages of 21 and 65 years.Fluent in English.Present with CLBP as their primary pain complaint (chronic low back pain is defined in the context of this study as having persisted at least 3 months and having resulted in pain on at least half the days in the past 6 months. We used the NIH Research Standards for Back Pain as a guide [45].Average back pain intensity reported at the time of the screening visit greater than or equal to 4 out of 10 during the preceding month.

The exclusion criteria are:Previous acupuncture treatment for any reason in the past 5 years. Participants with recent acupuncture exposure are more likely to recognize real as compared to sham EA and become unblinded, thereby increasing bias in the outcome. We therefore elected to exclude those with recent acupuncture experience to help minimize unblinding and reduce bias.Any radicular symptoms; any identified spinal nerve root or spinal cord disease contributing to back pain; co-morbid pain syndrome (secondary pain complaint not exclusionary if less severe).Ongoing legal or disability claim, worker’s compensation (permanent and stationary disability not exclusionary)Currently pregnant or planning to become pregnant.Medical conditions that would interfere with study procedures (e.g., heart disease or pacemaker, active infection, current cancer diagnosis; bleeding disorders).Psychiatric disorders, indicated by the Mini International Neuropsychiatric Interview (MINI) (version 7.0, including
○ Major depressive episode: current (2 weeks)○ Suicidality: current (past month)○ Manic episode: current○ Hypomanic episode: current○ Post-traumatic stress disorder (PTSD): current (past month)○ Alcohol use disorder: past 12 months○ Substance use disorder: past 12 months○ Psychotic disorders: lifetime○ Mood disorder with psychotic features: current○ Anorexia nervosa: current (past 3 months)○ Bulimia nervosa: current (past 3 months)○ Antisocial personality disorder: lifetime
Medications: starting new medical treatment or medication for pain 2 months prior to initiation of study procedures (participants who start such treatment after enrollment will be discontinued); opioids (≥ 60 mg morphine equivalent units/day), benzodiazepines, beta-blockers, some antipsychotics, diabetic medications, other medications that may interfere with study procedures, determined at the discretion of the study team; (selective serotonin reuptake inhibitors, anticonvulsants, and thyroid medications are not exclusionary, but tricyclic antidepressants and serotonin and norepinephrine reuptake inhibitors will be excluded); blood thinners (e.g., Coumadin, Plavix), at the discretion of the study team.

